### **Systematic CNS MRI imaging to document early/manifest encephalitic changes in COVID-19 patients.**

Both patient populations will undergo 3 Tesla magnetic resonance imaging (MRI) in collaboration with our colleagues from neuroradiology (responsible: [name]). MRI sequences will include 3D T1 +/- gadolinium, FLAIR, diffusion, SWI and T2 weighted sequences to document potential early signs of encephalopathy, and will be correlated to CSF, plasma and clinical findings. Appropriate precautions will be taken to ensure the safety in the MRI scanner of patients with respiratory, neurological, or other types of dysfunction, and all necessary anti-infectious precautions will be observed before, during, and after the scanning of patients with known COVID infection.

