## **3 PROJECT POPULATION AND STUDY PROCEDURES**

### **3.1 Project population, inclusion and exclusion criteria**

We will *prospectively* include 20 non-critically ill COVID-19 patients from the inpatient ward or from the ambulatory test centre, and 20 critically ill COVID-19 patients needing mechanical ventilation at the ICU. Neurological assessment will be performed by a board-certified neurologist using NIHSS (National Institute of Health Stroke Scale) scoring and other standard neurological tests. Neurological symptoms will be carefully documented. Assuming a case fatality rate of 50% in the critically ill group, we anticipate to include 10 patients for *post mortem* analysis of brain regions, some of which might be neurologically affected.

The following inclusion criteria are going to be applied: COVID-19 positive tested.

The following exclusion criteria are going to be applied: COVID-19 negative tested, patients under 18 years old, pregnant women.

A pregnancy test is performed and documented for women of childbearing age

Concerning the out-patients they will only be included if they have the option to come to the hospital by car, bike or if they live close enough to walk. In case public transport is their only option they can not be included.

To avoid conflicts and to identify parallel participation of individual USB patients in several studies, the DKF (Departement Klinische Forschung) has created a web application.

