## **4 STATISTICS AND METHODOLOGY**

### **4.1. Statistical analysis plan**

This study encompasses a multidimensional exploratory data set of both clinical and biological data. In this Project we are going to collect data sets of 40 participants.

*MRI data:* Imaging data will be analysed by board certified neuroradiologists, and specific encephalitic changes that might be COVID-19 related, will be reported and conjoined with potential neurological symptoms depending on the location of the potential encephalitic lesions. Most importantly, patients that are neurologically affected will be compared to non-affected individuals in terms of CNS involvement.

*Proteomic analysis:* The proteomic biomarkers from an array of cytokines and other inflammatory mediators (CSF and plasma, provided by the company Olink.com) will be compared to control reference sample using descriptive statistics and multivariate comparisons such as clustering algorithms, heatmaps, and correlative analysis. Furthermore, potential treatment effects from antiviral drugs or immune modulators might be taken into considerations.

*Cytof analysis:* Mass cytometry will be performed form peripheral blood mononuclear cells and analyzed with specific platoforms such as immune-Atlas and FlowJo software. High dimensional nearest neighbourhood analysis will be performed (tSNE plots). Cell population frequency and marker expression profile will be potentially correlated to the presence/absence of neurological symptoms and the respective cytokine profile.

*CODEX analysis:* Brain region from deceased patients will be fixed, paraffin embedded and subjected to the CODEX workflow by staining with a 50+ Marker panel. This is followed by a complex analysis pipeline which generates single-cell information of specific cell types derived from the multicycle image acquisition. Images will be segmented, cleaned-up, and cells will be clustered in supervised and unsupervised manner. Global and single marker expression per cell type will be assessed. Cellular neighbourhoods combined with viral distribution will be analyzed. This pipeline is currently implemented at the Department of Biomedicine and pathology and subject to ongoing modifications.

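### The main affected versus non-affected comparison, and the CyTOF correlations with neurological symptoms, take no account of the two severity cohorts, so a marker of critical illness can pass for a marker of CNS involvement

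*Protocol*

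**What the plan says.** Section 3.1 enrols two groups of equal size from opposite ends of the severity range. The milder group is described as "20 non-critically ill COVID-19 patients from the inpatient ward or from the ambulatory test centre". The severe group, of the same size, is defined by its setting and respiratory support: "20 critically ill COVID-19 patients needing mechanical ventilation at the ICU". Neurological status is assessed "using NIHSS (National Institute of Health Stroke Scale) scoring and other standard neurological tests". Section 2.3 sends both groups to imaging: "Both patient populations will undergo 3 Tesla magnetic resonance imaging (MRI").

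The analysis is set out in section 4.1, which calls the data set exploratory and gives the total: "In this Project we are going to collect data sets of 40 participants". Under MRI data it states the comparison it ranks highest: "Most importantly, patients that are neurologically affected will be compared to non-affected individuals in terms of CNS involvement". Under CyTOF it adds: "Cell population frequency and marker expression profile will be potentially correlated to the presence/absence of neurological symptoms and the respective cytokine profile".

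Neither sentence mentions cohort, severity or ventilation. The only third variable in section 4.1 is drug treatment, which is optional and appears only in the proteomics paragraph. The reference CSF and plasma samples described in section 2.3 come from healthy COVID-19 negative people.

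**The concern.** The study selects patients on severity and then analyses them on a different axis. If ventilated patients are more often neurologically affected, and also differ in cytokines, cell frequencies or MRI appearance because they are critically ill, the two variables will be associated across the 40 patients even when they are unrelated within each cohort.

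This bears on the study's stated purpose. Section 2.2 makes the correlation of clinical state with imaging and laboratory data the primary endpoint, and looks to it for biomarkers of CNS involvement that could guide treatment. A pure severity marker would meet that description. The healthy reference samples cannot settle the matter, because they differ from the ICU patients in critical illness as well as in infection.

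**Working it through.** **Inputs from the protocol.** Cohort sizes are 20 and 20 (section 3.1), and 20 + 20 = 40 agrees with the total in section 4.1. The expected autopsy number also reproduces: 50% × 20 = 10 (section 3.1). The protocol gives no significance level, effect size, or expected rate of neurological or MRI abnormality. Everything below therefore rests on assumed values, shown as a range, with a two-sided 5% level used only as a yardstick.

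**Check 1: continuous marker and continuous neurological score.** Assume equal cohorts, zero correlation within each, and a between-cohort difference of d within-cohort SDs on both variables. Mixing the cohorts adds d²/4 to each variance and to the covariance, so

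overall r = (d²/4) / (1 + d²/4).

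- d = 1: 0.25 / 1.25 = 0.20
- d = 1.5: 0.5625 / 1.5625 = 0.36
- d = 2: 1 / 2 = 0.50

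Simulation of 40,000 data sets of 20 + 20 gives the share of studies with a positive test:

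| d | expected r | cohorts ignored | cohort adjusted |
|---|---|---|---|
| 1 | 0.20 | about 24% | about 5% |
| 1.5 | 0.36 | about 67% | about 5% |
| 2 | 0.50 | about 96% | about 5% |

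**Check 2: yes/no MRI abnormality by neurological status.** This is closer to the MRI sentence in section 4.1. Let a be the probability of being affected and m the probability of an abnormal MRI, independent within each cohort (true odds ratio 1). With equal cohorts, taking a = 0.8 (ICU) and 0.2 (other), and m = 0.6 and 0.1:

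- abnormal among affected: (0.8 × 0.6 + 0.2 × 0.1) / (0.8 + 0.2) = 0.50
- abnormal among non-affected: (0.2 × 0.6 + 0.8 × 0.1) / (0.2 + 0.8) = 0.20
- overall odds ratio: (0.50/0.50) / (0.20/0.80) = 4.0

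The same arithmetic gives the odds ratios below. The percentages come from 20,000 simulated studies per row, with Fisher's exact test ignoring cohort and an exact conditional test stratified by cohort.

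| a, ICU/other | m, ICU/other | overall OR | cohorts ignored | stratified |
|---|---|---|---|---|
| 0.5/0.5 | 0.5/0.1 | 1.0 | 3.1% | 2.9% |
| 0.6/0.3 | 0.4/0.1 | 1.6 | 6.5% | 2.8% |
| 0.7/0.2 | 0.5/0.1 | 2.6 | 22.6% | 2.7% |
| 0.8/0.2 | 0.6/0.1 | 4.0 | 44.3% | 2.2% |
| 0.9/0.1 | 0.6/0.1 | 6.9 | 72.3% | 1.6% |

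The first row shows the limit: when neurological status does not differ by cohort, there is no inflation, even though MRI findings do differ.

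**The case against.** Five points can fairly be made on the other side.

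- **Pooling is not stated.** The protocol never says that the cohorts are merged, and section 2.3 refers to both groups when it describes who is assayed and scanned. A separate analysis plan might add strata. This stands in part. The reading is an inference, but section 4.1 carries the title of the analysis plan, names the comparison as the leading one, and defines it on an axis that cuts across the recruitment groups.
- **No test is specified.** The study is exploratory and descriptive, and the CyTOF correlation is worded as a possibility. This stands: the percentages are a yardstick, and the harm is a misattributed biomarker, not a failed confirmatory test. Exploratory status does not remove confounding.
- **The cohort differences are assumed.** This stands. The protocol documents only ICU status and ventilation as separating the groups. A reader might infer that age, comorbidity and sedation also differ; the protocol does not say so. Nor do its lists of recorded data (sections 3.3 and 7.2) name age or sex.
- **Stratifying may remove real signal.** Sections 2.1 and 2.3 hypothesise that CNS effects contribute to brainstem dysfunction and respiratory failure. Ventilation could then be partly a result of CNS involvement, and conditioning on cohort would remove some of the effect sought. This stands, and it rules out the stronger demand that the unstratified contrast be dropped.
- **Not every analysis is affected.** A reader might extend the point to all biomarker analyses. CODEX uses autopsy cases expected from the critically ill group ("Assuming a case fatality rate of 50% in the critically ill group, we anticipate to include 10 patients for" post mortem study), so it is already effectively within one cohort. The proteomic comparison with reference samples is a different contrast.

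**Conclusion.** The concern holds in a limited form. As written, section 4.1 allows critical illness to appear as CNS involvement in the affected versus non-affected comparison and in the CyTOF and cytokine correlations with neurological symptoms. The possible size ranges from nothing to large: none if neurological status is alike in the two cohorts, a positive test in about 72% of studies in the most extreme MRI scenario, and about 96% when marker and score both differ by 2 SD. All of these rest on assumed cohort differences, no within-cohort association and a nominal 5% test that the protocol does not set.

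A reader might infer that the protocol prescribes a pooled analysis, or that its conclusions are bound to be spurious. The text supports neither: it is silent on cohort, and the rates that decide the size are unknown. This is something the sponsor should fix, at low cost, not a fatal flaw.

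**What to change.** Add one paragraph to section 4.1:

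- Report the affected versus non-affected comparison, and the CyTOF and CSF/plasma correlations with neurological status, within each cohort and as a cohort-stratified or cohort-adjusted estimate.
- Show the unstratified estimate beside them, labelled as not separable from critical illness.
- If nearly all patients in a cohort share the same neurological status, state that the within-cohort contrast is not estimable, and do not interpret the unstratified one as specific to the CNS.
- Age may be added where it is recorded. CODEX needs no cohort term.

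Cohort is known at enrolment, so no new visit, sample or measurement is needed. There are two costs. Intervals will be wider, most of all when neurological status nearly coincides with cohort. The stratified estimate may also lose some true signal if ventilation is itself a consequence of CNS involvement, which is the reason for showing both.

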## 2.3 Project design

The project flowchart is depicted below. Patients with confirmed COVID-19 disease specifically hospitalized for this disease as well as out-patients will be included. After patient informed consent, we will perform a detailed clinical-neurological assessment followed by blood and lumbar puncture, and MRI analysis. In case of disease-related death (assuming a case fatality rate on the ICU of 50%), an autopsy by the institute of pathology will be performed, encompassing high dimensional analysis of the organs under investigation.

[figure not shown]

**CSF and plasma cytokine proteomics and correlate to mental/neurological state.** CSF will be acquired by lumbar puncture and sent for routine analysis including CSF chemistry, cytology and microbiology. Targeted CSF proteomics using OLINK Proximity Extension Assay (PEA) technology (<https://www.olink.com/products/immune-response-panel/>), to assess a potential

CNS-contribution of the disease will be performed. A similar biomarker approach will be applied for plasma samples from the same time-point as the lumbar puncture. Already established CyTOF technology will be used to gain insight into the peripheral blood immune composition in both patient cohorts (CyTOF panel listed in table 3). Presence of viral RNA will be tested by our in-house qPCR in both plasma and CSF. We will include COVID-19 negative CSF and plasma samples from healthy reference patients into this analysis.

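### The reference samples have no age or sex rule and the marker comparisons named in 4.1 do not condition on age or sex, so differences from the reference may reflect age or sex rather than COVID-19

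*Protocol*

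**What the plan says.** Protocol 4.1 (proteomic analysis) states that the CSF and plasma markers "will be compared to control reference sample using descriptive statistics and multivariate comparisons such as clustering algorithms, heatmaps, and correlative analysis". The only other influence it mentions is antiviral or immunomodulatory treatment, and that only as something that might be considered. Age and sex are not named as analysis variables.

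The reference group is described in 2.3: "We will include COVID-19 negative CSF and plasma samples from healthy reference patients into this analysis". The same sentence recurs under the CyTOF heading of 2.3. Neither place gives a number, a source, an age range, a sex balance or a matching rule.

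The eligibility rules in 3.1 do not fill the gap. They exclude "COVID-19 negative tested, patients under 18 years old, pregnant women". COVID-19 negative people are thus outside the enrolled population, so the age limit of 18 is a rule for patients and is not stated for the reference samples. Two groups of 20 are enrolled. One consists of ward patients or out-patients who are not critically ill. The other is described as "20 critically ill COVID-19 patients needing mechanical ventilation at the ICU".

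A separate sentence in 4.1, under MRI data, states that "patients that are neurologically affected will be compared to non-affected individuals in terms of CNS involvement". It names no statistical method and does not involve the reference samples.

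**The concern.** The comparison with the reference is not randomised. The COVID-19 participants are ventilated ICU patients, ward patients and out-patients who volunteer. The reference samples come from healthy people with no stated link to any of these. Nothing in the design keeps age or sex comparable. If a protein varies with age and the two sides differ in age, an unadjusted comparison shows a difference even when SARS-CoV-2 has no effect on that protein. The same holds for sex.

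This matters because of what the comparisons are for. Section 2.2 makes the integration and correlation of these data the primary endpoint and expects markers that foretell CNS involvement and help to direct treatment. A protein that stands out because one group is older is not such a marker. Calling the data set exploratory does not remove confounding; it only limits how firmly the result may be stated.

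**Working it through.** **The plan's own figure.** 4.1 states: "In this Project we are going to collect data sets of 40 participants". The groups in 3.1 give 20 + 20 = 40, which agrees. The reference samples are not part of this count, and no number is given for them. The protocol states no alpha, power, effect size or SD, so there is no power calculation to reproduce.

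**Inputs for the illustration.** All are assumptions, because the documents supply none of them:
- d, the difference in mean age between the groups, in within-group SD units
- r, the within-group correlation of marker with age
- no true group effect; a two-sided 5% comparison
- group sizes: 20 versus 20, with two alternatives below

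**Step 1: spurious difference.** With no disease effect, the expected standardised difference is r × d.

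**Step 2: chance of declaring a difference, 20 versus 20.** Use the non-central t distribution with 38 degrees of freedom and non-centrality r × d × √(20 × 20 / 40) = r × d × 3.162.

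| d | r | r × d | Non-centrality | False-positive rate |
|---|---|---|---|---|
| 0.5 | 0.2 | 0.10 | 0.32 | 6.1% |
| 1.0 | 0.3 | 0.30 | 0.95 | 15.2% |
| 1.0 | 0.5 | 0.50 | 1.58 | 33.8% |

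The normal approximation gives 6.2%, 15.8% and 35.3%. With d = 0 the rate is 5% whatever r is.

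**Step 3: other group sizes.** 20 versus 20 is the size of the severity split, not of the comparison with the reference, whose size is unknown. By the normal approximation, with standard error √(1/n₁ + 1/n₂) and d = 1:
- 40 patients versus 20 reference samples: 19.5% (r = 0.3), 44.7% (r = 0.5)
- 20 patients versus 10 reference samples: 12.1% (r = 0.3), 25.2% (r = 0.5)

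The pattern is the same, and the figure moves with the unstated reference number.

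**Step 4: does adjustment help?** In 4,000 simulated data sets per setting (20 versus 20), the unadjusted t test rejected in 14.8% at d = 1, r = 0.3 and in 34.5% at d = 1, r = 0.5. With age in a linear model the rates were 4.7% and 5.4%. A partial correlation given age gave the same rates as the model.

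**Step 5: what adjustment costs.** For equal groups, the collinearity of group and age multiplies the variance of the group contrast by 1 + d²/4: 1.06 at d = 0.5, 1.25 at d = 1, 2.0 at d = 2. At d = 1 the interval is √1.25 = 1.12 times as wide, before any gain from the marker variation that age explains. Matching that brings d to 0 avoids this cost.

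**The case against.** The strongest reply has four parts.

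1. *The method list is open.* It gives examples: "using descriptive statistics and multivariate comparisons such as clustering algorithms, heatmaps, and correlative analysis". Descriptive statistics can be stratified, and correlative analysis can include partial correlation, which restores the 5% rate in step 4. This stands. A reader might infer that the named methods cannot hold age or sex constant. The text supports only that, as named, they do not.

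2. *Covariate choice commonly belongs in a SAP, and none is shown.* This stands for adjustment taken alone, whose absence would be no finding. It does not cover the choice of reference samples. That is a design step: if the samples are drawn with little overlap in age, a later model can repair the comparison only at a loss of precision or by extrapolation.

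3. *No imbalance is documented.* This also stands. A reader might infer that age differences will be taken for COVID-19 effects, or that the reference patients are picked without regard to age. The protocol gives no ages and is silent on how they are picked. An imbalance is a plausible risk, and the illustration shows little harm if the age gap or the correlation is small.

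4. *The MRI contrast is a different matter.* A reader might carry the point over to the affected versus non-affected comparison and call it biased by the reference group or by the listed methods. It uses neither. It also rests on neuroradiologists' reading of specific encephalitic changes and their location, not on general background change. Age may still differ between those groups, so reporting it is sensible, but the documents do not show that this contrast is biased.

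**Conclusion.** The point holds for the comparison with the reference samples. The protocol sets no age or sex rule for them, and the comparisons it names do not condition on either. A difference from the reference therefore cannot be attributed to COVID-19 unless age and sex are balanced or adjusted for.

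The size of the bias cannot be determined from the documents. On the stated assumptions, the false-positive rate per marker is close to nominal (about 6%) for a small age gap and weak correlation, and three to seven times nominal (about 15% to 34%) at a 1 SD gap with correlations of 0.3 to 0.5. These figures show what can happen; they do not estimate what will happen in this study. They treat age only; sex was not quantified.

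The change should be made before the reference samples are chosen, since that step is the hardest to repair afterwards. The point does not invalidate the study or its exploratory aim.

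**What to change.** **In 2.3:** state the source and number of the reference samples. Select them frequency-matched to the COVID-19 participants on age band and sex, as far as available samples allow. Record age and sex for each; the protocol does not say that they are known for these samples.

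**In 4.1:**
- Estimate each protein and cell-population contrast with a linear model containing group, age and sex (log scale for proteins), with 95% intervals, labelled exploratory.
- Keep heatmaps and clustering as descriptive displays, annotated by age and sex. Do not run them on residualised values: residuals from a pooled model without group remove part of a true group effect when age and group are correlated.
- For the affected versus non-affected comparison, report age and sex by group and adjust for age where numbers allow.

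**Cost:** a few sentences; some restriction in the choice of reference samples; and wider intervals if ages still differ after matching (variance factor about 1.25 at a 1 SD gap). No new patient procedure is needed. Age and sex may have to be retrieved for the reference samples, and matching may be incomplete if few are available.

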## **4.2. Handling of missing data**

We assume to have complete data from blood, CSF and MRI analysis from all the participating patients. If for some reason the dataset is not complete, this will be reported in the data analysis.

# **5 Regulatory Aspects and Safety**

## **5.1 Local regulations / Declaration of Helsinki**

This research project will be conducted in accordance with the protocol, the Declaration of Helsinki [3], the principles of Good Clinical Practice, the Human Research Act (HRA) and the Human Research Ordinance (HRO) [1] as well as other locally relevant regulations. The Project Leader acknowledges his responsibilities as both the Project Leader and the Sponsor.

